### 7.3. Reporting of AEs, SAEs and SUSARs

Any AE that meets any criterion for an SAE defined in section 7.1.2 requires the completion of an SAE Report Form in addition to being recorded on the AE page of the eCRF, regardless of causal relationship to the study drug. SAEs occurring after EoS will only be reported in case the investigator suspects a relation to study drug.

Where possible, a diagnosis rather than a list of symptoms should be given. The investigator is responsible for assessing seriousness, severity, and causality of the SAE. The SAE form should be completed with as much information as possible. The investigator should not wait for full details before making the initial report.

According to national and international legislation all SAEs, which have been identified as SUSAR, will be reported to the respective competent authorities (CA) and ethics committee (EC).

#### 7.3.1. Time Period and Frequency for Detecting AEs, SAEs and SUSARs

For this study, collection of all AEs will begin after providing written informed consent for participation in the study until the EOS visit.

#### 7.3.2. Timeframe for Reporting SAEs to Sponsor

Immediate reporting should allow the sponsor to take the appropriate measures to address potential new risks in the clinical trial. Therefore, the immediate report after knowledge of a SAE should be made by the investigator within a very short period of time and under no circumstances should this exceed 24 hours following knowledge of the serious adverse event. The investigator must report the SAEs within 24 hours of knowledge by fax or other appropriate methods (e.g. via e-mail) on the SAE form to the sponsor. Personal data has to be replaced by the trial subject number before forwarding any information to the sponsor.

#### 7.3.3. Documentation of AEs and SAEs and Follow-Up Procedure

AEs and SAEs will be documented in the eCRF with frequency, seriousness and severity, as well as the actions taken in relation to the AE (medication or other treatments). All SAEs should be followed up until clinical recovery is complete, stable condition is reached or the subject is lost to follow-up.

### 7.4. Laboratory Abnormalities

A clinical laboratory abnormality should be documented as an AE if any of the following conditions is met:

- judged to be of significant clinical importance
- results in discontinuation of the study
- abnormality is of a degree that requires active management.

[figure not shown]

Laboratory abnormalities that meet the criteria for AE should be followed until they have returned to normal or an adequate explanation of the abnormality is found. A Grade 3 or 4 event (severe) as per CTCAE does not automatically indicate a SAE unless it meets the definition of serious as defined above.

## 7.5. Contraception

Reproductive toxicity and teratogenicity data are not sufficiently reliable for the investigational drug. As this study enrolls women as well who are considered to be of childbearing potential, all suitable measures must be taken to avoid falling pregnant. Male participants and female participants of childbearing potential must maintain highly effective contraception methods starting from signing of the informed consent form and for at least 3 months after the last dose of study treatment.

Highly effective methods of birth control for female participants and female partners of male participant who are able to become pregnant include the methods below (according to the CTFG Recommendations related to contraception and pregnancy testing in clinical methods with a failure rate of less than 1% per year):

- Total abstinence from heterosexual intercourse (when this is in line with the preferred and usual lifestyle of the subject). Periodic abstinence (e.g. calendar, ovulation, symptothermal, post-ovulation methods) and withdrawal are not acceptable methods of contraception.
- Female sterilization (surgical bilateral oophorectomy with or without hysterectomy), total hysterectomy or tubal ligation at least six weeks before taking investigational drug. In case of oophorectomy alone, only when the reproductive status of the woman has been confirmed by follow up hormone level assessment.
- Male sterilization (at least 6 months prior to drug intake). For female subjects on the study the vasectomized male partner must be the sole partner for that woman.
- Use of oral (estrogen and progesterone), injected or implanted hormonal methods of contraception by woman with correct and consistent use or placement of an IUD or intrauterine system (IUS) or other forms of hormonal contraception that have comparable efficacy (failure rate <1 %), for example hormone vaginal ring or transdermal hormone contraception. In case of use of oral contraception, women should be stable on the same product for a minimum of 3 months before taking investigational drug. In addition to hormonal contraception method by woman, the male sexual partner should use a barrier method (e.g. condom).

Men must avoid sperm donation for up to 90 days after treatment

## 8. Statistical Analysis

All medical terms reported as adverse events (AE) are coded according to the Medical Dictionary for Regulatory Activities (MedDRA) for safety analysis. At least the primary System Organ Class (SOC) as well as the Preferred Term (PT) will be available for the statistical analysis. Incidences of AEs will be summarized by intensity and relationship to the study drug.

Descriptive statistics will be calculated for plasma concentration of niclosamide at each applicable time point specified, and for the derived plasma PK parameters.

The primary PK parameters are  $C_{max}$ ,  $AUC_{last}$  and  $AUC_{inf}$ ,  $C_{8h}$ ,  $C_{12h}$ ,  $C_{24h}$ ,  $T_{1/2}$ .

The food effect evaluation in Part A and the relative bioavailability compared to the chewing tablets in Part B will be performed using a linear fixed effect model containing fixed effects for sequence, treatment, period and subjects within sequence for log-transformed  $C_{max}$ ,  $AUC_{last}$

[figure not shown]

and AUCinf, respectively. Only subjects with evaluable data for both periods. The point estimate of the ratio of geometric means (fed/fasted; oral solution/chewing tablets) will be provided together with a 90% confidence interval

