| Statistical Analysis:             | 
All medical terms reported as adverse events (AE) are coded according to the Medical Dictionary for Regulatory Activities (MedDRA) for safety analysis. At least the primary System Organ Class (SOC) as well as the Preferred Term (PT) will be available for the statistical analysis. Incidences of AEs will be summarized by intensity and relationship to the study drug.
 
For each treatment, descriptive statistics will be calculated for plasma concentration of niclosamide at each applicable time point specified, and for the derived plasma PK parameters.
 
The primary PK parameters are <math>C_{max}</math>, <math>AUC_{last}</math> and <math>AUC_{inf}</math>, <math>C_{8h}</math>, <math>C_{12h}</math>, <math>C_{24h}</math>, <math>T_{1/2}</math>.
 
The food effect evaluation in Part A and the calculation of the relative bioavailability compared to the chewing tablets in Part B will be performed using a linear fixed effect model containing fixed effects for sequence, treatment, period and subjects within sequence for log-transformed <math>C_{max}</math>, <math>AUC_{last}</math> and <math>AUC_{inf}</math>, respectively. Only subjects with evaluable data for both periods will be evaluated. The point estimate of the ratio of geometric means (fed/fasted; oral solution/chewing tablets) will be provided together with a 90% confidence interval.
 |

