### Part A: Single ascending dose (SAD)

Four subjects per cohort will be randomized to receive a single oral dose of the niclosamide solution or matching placebo in a 3:1 ratio.

The SAD cohorts are planned as follows:

*Cohort A1:* 200 mg (fasted conditions)

*Cohort A2:* 600 mg (fasted conditions)

*Cohort A3:* 1600 mg (fasted and fed conditions)

Dose escalation will only be performed with the niclosamide solution if the previous dose was safe and the plasma concentration of above 5µM after 8 hours has not been reached in all subjects in a cohort. If the 1600 mg is not tolerated there is an option to decrease the dose to 1200 mg niclosamide solution.

The last dose cohort (A3) will be repeated in the same subjects under fed conditions. The subjects will be dosed under fed conditions if the cohort A3 under fasted condition is safe and well tolerated (based on 48 hrs safety data) and PK data is available.

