### SAD Part visits design:

Part A of this study is comprised of a screening visit (between Day -21 and -2), a baseline visit (Day -1), a treatment visit with a single dose of niclosamide solution or placebo (Day 1), and an End of Study (EOS) visit (between Day 4 and 6).

Subjects will remain domiciled in the study site from Day -1 until the Day 2 (24h post dose) and until assessments have been completed. Subjects will be allowed to leave the study center on Day 2 (safety signals, if any, are expected to occur within 24h from the drug administration, due to the expected short half-life of niclosamide solution) at the discretion of the Investigator, if there are no prohibitive safety findings. The subjects will be asked to return to the study site for the EOS assessments on Day 4 (+2 days). The EOS evaluation has also to be performed if a subject prematurely terminates the study for any reason.

All baseline safety evaluations results must be available prior to dosing. Subjects will fast  $\geq 9$  hours overnight between Day -1 and Day 1 pre-dose and remain fasted 4 hours post-dose on Day 1. Subjects will be randomized to receive either the niclosamide solution or matching placebo, depending on the randomization assignment.

Cohort A3 will be repeated in the same subjects under fed conditions (high fat breakfast). The subjects will be dosed under fed conditions as soon as the PK is available and safety data for 48 hrs, however not shorter than 5 half-lives based on the PK results of cohort A3 fasted conditions.

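### The food-effect model set for Part A cannot identify the fed/fasted ratio, because every A3 subject is dosed fasted first and fed second

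*Protocol*

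**What the plan says.** Section 8 of the protocol assigns one analysis to two comparisons, the food effect in Part A and the solution-versus-tablet comparison in Part B. It is a "linear fixed effect model containing fixed effects for sequence, treatment, period and subjects within sequence", and it is to be applied to Cmax, AUClast and AUCinf on the log scale. The Synopsis (Statistical Analysis) repeats it, again "containing fixed effects for sequence, treatment, period and subjects within sequence". The output is also fixed: "The point estimate of the ratio of geometric means (fed/fasted; oral solution/chewing tablets) will be provided together with a 90% confidence interval". The data are restricted: "Only subjects with evaluable data for both periods". No other food-effect model is given.

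Only cohort A3 in Part A is dosed under both conditions. Section 3.1 (Part A) says: "The last dose cohort (A3) will be repeated in the same subjects under fed conditions". Fed dosing follows only if fasted dosing proves safe and well tolerated, and only once the fasted PK results are known (section 3.1; Table 1, footnote 1). The randomisation in Part A concerns drug or placebo, not the order of conditions: "Four subjects per cohort will be randomized to receive a single oral dose of the niclosamide solution or matching placebo in a 3:1 ratio".

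Part B, by contrast, randomises subjects to two sequences (solution then tablet, or tablet then solution) with two subjects planned in each.

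**The concern.** A model with both treatment and period effects can separate them only if some subjects take the treatments in the opposite order. Part B meets that condition and A3 does not. In A3, period 1 is always fasted and period 2 is always fed, so the two effects cannot be told apart, and a sequence term has nothing to estimate. The Part B model appears to have been applied to a design that cannot support it.

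Three things are at stake. First, an analyst who follows the text obtains either a non-estimable contrast or a number that depends on software defaults. Second, a reader would take any printed fed/fasted ratio as adjusted for period, when it would contain the whole of any period or order effect. Third, the comparison is used: section 3.1 (Part B) bases fed dosing in Part B on the Part A PK results, and the Amendment 2 rationale says that feeding cost no bioavailability. Part C is also run fed.

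**Working it through.** **Inputs.** Model terms: section 8 and Synopsis. Order of conditions in A3: section 3.1 and Table 1, footnote 1. Subjects with niclosamide PK: 4 randomised 3:1, so 3 on niclosamide (section 3.1). Part B layout: section 3.1, cohort B1 table. The protocol gives no within-subject CV, so the values in step 5 are assumptions. It states no figure to reproduce here.

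**Step 1: the A3 design matrix.** 3 subjects × 2 periods = 6 rows. Columns: intercept, sequence, fed, period 2, and one indicator per subject, 7 in all. Three exact dependencies hold:

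- sequence = intercept, as there is one sequence;
- period 2 = fed, row by row;
- the three subject indicators sum to the intercept.

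Rank = 7 − 3 = 4.

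**Step 2: estimability.** Let τ be the fed effect and π the period effect on the log scale. For every subject

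E[log(fed) − log(fasted)] = τ + π.

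Replacing (τ, π) by (τ + d, π − d) leaves every fitted value unchanged for any d, so the data identify only the sum. As a numerical check, τ is estimable only if adding its contrast row leaves the rank unchanged. Here the added row raises the rank from 4 to 5.

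**Step 3: variants, checked numerically.**

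| Layout and model | Observations | Rank | Residual df | Treatment contrast estimable? |
|---|---|---|---|---|
| A3, 3 subjects, as written | 6 | 4 | 2 | No |
| A3, 3 subjects, sequence dropped, period kept | 6 | 4 | 2 | No |
| A3, 3 subjects, condition + subject only | 6 | 4 | 2 | Yes |
| A3, 4 subjects, as written | 8 | 5 | 3 | No |
| Part B, 4 subjects, as written | 8 | 6 | 2 | Yes |

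The number of subjects is not the cause: a fourth subject in the same order changes nothing. Dropping sequence alone does not help either; the period term must go.

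**Step 4: what software could return.** If period is dropped, the treatment coefficient estimates τ + π. If treatment is dropped, there is no food effect to report. A routine that checks estimability will flag the contrast. The stated model does not say which of these is intended.

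**Step 5: the paired model.** With condition and subject only, the estimate is the mean of 3 within-subject log differences. With s_w = √ln(1 + CV²), its standard error is s_w·√(2/3). The 90% limits are the ratio divided and multiplied by

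exp(t₀.₉₅,₂ × s_w × √(2/3)), with t₀.₉₅,₂ = 2.920.

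| Assumed within-subject CV | s_w | Factor |
|---|---|---|
| 30% | 0.294 | 2.01 |
| 50% | 0.472 | 3.08 |
| 100% | 0.833 | 7.28 |

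For the 50% row: 2.920 × 0.472 × 0.816 = 1.126, and exp(1.126) = 3.08.

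**The case against.** The case for leaving the text alone has five parts.

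- **The food effect is a secondary objective in a descriptive study.** Section 8.1 plans no formal hypothesis test, and no decision threshold is attached to the ratio. This stands and limits the consequence. It does not make the contrast estimable, and section 8 still promises a point estimate and an interval.
- **The SAP may already use another model.** It may; it was not available for this review. It could do so only by departing from the model that the protocol states twice.
- **Software that drops period returns the paired estimate anyway.** True. The ratio is not beyond estimation. But it then rests on an assumption of no period effect that the protocol never states, and that the stated model contradicts by including a period term.
- **Period effects are probably small.** Fed dosing waits for 48 h safety data and at least 5 half-lives. At 5 half-lives, 0.5⁵ ≈ 3% of drug remains. With the upper half-life of 5 h in the Amendment 2 rationale, 48 h is 9.6 half-lives and about 0.1% remains. Drug carry-over is therefore minor, but other period or order effects are not excluded.
- **The choice of fed conditions did not rest on a modelled ratio.** The protocol cites Part A PK results and better average tolerability, not a model-based interval, and the decision was already taken in Amendment 2. This stands: correcting the model will not reverse that decision. It affects how the supporting evidence is reported.

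The interval widths in step 5 come from having three pairs, and the corrected model has the same widths. They show how little the comparison can say; they do not measure the model error.

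**Conclusion.** The concern holds. As written, the model for the Part A food effect is rank-deficient (rank 4 of 7 columns), and the fed/fasted ratio that section 8 promises is not estimable in it. This follows from the fixed fasted-then-fed order alone and needs no assumption about variability or sample size. The same model is sound for Part B.

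A fed/fasted ratio can still be obtained from a paired analysis of the 3 niclosamide subjects, on 2 degrees of freedom, provided that no period effect is assumed. Under CVs of 30% to 100%, which are assumed and not taken from the protocol, the 90% limits lie a factor of about 2.0 to 7.3 either side of the ratio. A claim that feeding costs no bioavailability would then be weakly supported, whichever wording is used. The text needs correcting because it prescribes an analysis that gives an undefined result; the consequence is moderate because the objective is secondary and descriptive.

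**What to change.** In section 8 and the Synopsis, separate the two analyses:

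- **Part B:** keep the model with sequence, treatment, period and subject within sequence.
- **Part A food effect:** log parameter = condition + subject, for A3 subjects on niclosamide with evaluable data under both conditions (planned n = 3), with no sequence or period term. Report the geometric mean ratio with its 90% interval on 2 degrees of freedom.
- **Label and caveat:** call the result the ratio of fed (second period) to fasted (first period), and state that the fixed order confounds food with period.
- **Presentation:** show the individual ratios beside the estimate, since three values are more informative than the interval alone.

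The cost is wording in the protocol and SAP; no subjects, visits or samples are added, and the dosing order is untouched. Part A data had already been evaluated when Amendment 2 was written, so the change should be dated and described as made after those data were seen. The food-effect result will claim less than an adjusted crossover ratio would, which is all the design supports.

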### 1.3. Rationale for Dose Selection

The niclosamide treatment regimen against tape worms comprises a 2 g dose at day 1 followed by 6 days of 1 g for individuals aged >6 years. Intestinal resorption is low, and the bioavailability is on average 10% (although there is a high variability).

Part A of the study consists of single ascending doses of the new oral solution with three planned cohorts (A1, A2, A3). The initial dose of 200 mg, in case of assuming 100% absorption, corresponds to the systemic exposure of the chewing tablet of 2000 mg assuming a bioavailability of 10%. However, complete (100%) absorption of the oral solution is highly unlikely since niclosamide is likely to be metabolized already in the intestine. The starting dose of 200 mg is therefore considered safe. The next higher dose of 600 mg is a threefold increase from the starting dose. The final dose of 1600 mg is limited by the solution excipients which are known to give rise to diarrhea at higher volumes. Both the 600 mg and 1600 mg cohorts will only be started if the previous dose is safe and the pre-defined plasma level of above 5  $\mu$ M (approx. 1.6  $\mu$ g/ml) after 8 hours has not been reached. If the 1600 mg dose is not tolerated, there is an option to repeat the cohort with a lower dose of 1200 mg. The last cohort will be repeated under fed conditions to investigate a possible food effect.

The first subject in each cohort will be the sentinel subject receiving an open label niclosamide solution administration.

Overall, the proposed SAD design for this study mimics conventional FIH studies, and thus, seems to be a suitably conservative approach for testing the niclosamide solution formulation.

Part B of the study compares the highest acceptable dose in Part A (1600 mg oral solution) with the highest approved dose of the chewing tablet (2000 mg) given as a QD dosing regimen under fed conditions to determine the relative bioavailability of the new oral solution formulation.

The chosen dose will not exceed the maximum tolerable dose in Part A.

Part C investigate safety and PK of the niclosamide solution over a period of 7 days.

This part consists of three groups: Group 1, 1200 mg niclosamide solution administered once daily, Group 2, 1600 mg niclosamide solution administered once daily and Group 3, placebo.

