### 2.1.2. Secondary Objectives

- To assess the PK of a single dose of the niclosamide solution under fed and fasted conditions in healthy volunteers (Part A)
- To assess saturation and/or dumping effects of niclosamide solution by dose escalation (Part A)
- To assess the relative bioavailability of the niclosamide solution compared to the already marketed chewing tablet administered as single dose under fed conditions in healthy volunteers (Part B)
- To assess the safety and PK of the niclosamide solution after multiple oral doses under fed conditions in healthy volunteers (Part C)

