### Part B (relative bioavailability compared to chewing tablets)

Planned doses:

- Single dose of 1600 mg oral niclosamide solution (highest dose that was tested to be safe and tolerable in Part A) under fed conditions
- Single dose of 2000 mg niclosamide chewing tablets as multiples of 500 mg chewing tablets under fed conditions

Part C (multiple doses of the niclosamide solution)

- Multiple doses of 1200 mg oral niclosamide solution under fed conditions over 7 days
- Multiple doses of 1600 mg oral niclosamide solution under fed conditions over 7 days
- Placebo under fed conditions over 7 days

In all cohorts, study drug will be administered at the study site.

In Part A cohorts, subjects must have fasted overnight for at least 9 hours before study drug intake. Intake of water is not allowed from approximately 2 hours before until approximately 2 hours after study drug intake (except for the non-carbonated water required for study drug intake). Standard lunch will be served within 15 to 30 minutes after the 4-hour PK sampling on Day 1 and in Part B also on Day 3. The lunch should be of the same composition for all subjects on Day 1. The standard lunches should be ingested entirely within 30 minutes. If this is not possible, the approximate percentage of the consumed food should be documented.

A standard snack and a standard dinner will be served approximately 7 and 10 hours postdose, respectively. This snack and dinner should be of the same composition for all subjects.

In the fed dose cohort in Part A (cohort 3) and in Part B and Part C, following overnight fast of at least 9 hours, subjects should start a high fat meal 30 minutes prior to the study drug administration at the study site between 7.30 and 10.00 AM. This meal should contain approximately 800 to 1000 calories and should derive approximately 150, 250, and 500 to 600 calories from protein, carbohydrate, and fat, respectively (according to the FDA guidance for industry). Subjects should consume the entire meal within 30 minutes. If this is not possible, the approximate percentage of the consumed food should be documented. Within 10 minutes after completing breakfast, but no more than 30 minutes from the start of their high fat meal, study drug will be administered with approximately 240 mL of non-carbonated water. Thereafter, subjects should receive standardized meals scheduled at the same time in each cohort of the study.

[figure not shown]

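### The Part B ratio labelled relative bioavailability compares 1600 mg with 2000 mg without dose-normalisation, so for AUC it estimates 0.80 times relative bioavailability

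*Protocol*

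**What the plan says.** Section 2.1.2 sets the only Part B objective: "To assess the relative bioavailability of the niclosamide solution compared to the already marketed chewing tablet administered as single dose under fed conditions". Section 1.3 says that Part B "compares the highest acceptable dose in Part A (1600 mg oral solution) with the highest approved dose of the chewing tablet (2000 mg", and gives the purpose as "to determine the relative bioavailability of the new oral solution formulation". Section 6.1.1 lists the two treatments as "Single dose of 1600 mg oral niclosamide solution (highest dose that was tested to be safe and tolerable in Part A" and "Single dose of 2000 mg niclosamide chewing tablets as multiples of 500 mg chewing tablets under fed conditions".

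Section 8 specifies a "linear fixed effect model containing fixed effects for sequence, treatment, period and subjects within sequence for log-transformed" Cmax, AUClast and AUCinf, followed by "The point estimate of the ratio of geometric means (fed/fasted; oral solution/chewing tablets) will be provided together with a 90% confidence interval". The synopsis repeats this and names the target outright: "the calculation of the relative bioavailability compared to the chewing tablets in Part B will be performed using a linear fixed effect model".

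The protocol is aware that the doses differ: the synopsis notes that 1600 mg is below the 2 g given as tablets. The only parameter that uses dose is CL/F, defined in the abbreviation list as Dose/AUCinf, and it is not a response variable in the ratio model.

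**The concern.** Relative bioavailability compares the fraction of each dose that reaches the circulation, so exposures must be divided by dose whenever the doses differ. The planned model does not do this. Its treatment effect mixes the formulation effect with the 1600/2000 dose ratio.

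The error has a fixed direction: it works against the solution. The solution was developed to give higher and more reproducible plasma levels than the tablet. Under the plan as written, a solution that is better per mg could be reported as equal to the tablet, and an equal one as delivering 20% less. The 90% confidence interval would be centred on the same wrong quantity.

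**Working it through.** The protocol gives no numerical figure for this ratio, so there is nothing to reproduce. The check runs from the definition.

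**Inputs.** Solution 1600 mg and tablet 2000 mg (Sections 3.1 and 6.1.1); four subjects, two per sequence (Section 3.1); log-scale fixed-effects crossover model with a 90% interval (Section 8).

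**1. Definition.** Let R be the planned AUC ratio, AUC(solution)/AUC(tablet). Then

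Frel = [AUC(solution)/1600] / [AUC(tablet)/2000] = R × 2000/1600 = 1.25 × R,

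so R = 0.80 × Frel.

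**2. Check against the protocol's own usage.** The synopsis and Section 1.3 treat bioavailability as a fraction of dose, on average 10% for the tablet: 0.10 × 2000 = 200 mg. A solution with the same 10% would deliver 0.10 × 1600 = 160 mg. The planned ratio would be 160/200 = 0.80 for two products of identical bioavailability.

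**3. What the planned ratio would show.**

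| True Frel | Planned ratio (0.80 × Frel) |
|---|---|
| 0.5 | 0.40 |
| 1 | 0.80 |
| 1.25 | 1.00 |
| 2 | 1.60 |
| 5 | 4.00 |

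**4. Effect on the interval.** log(AUC/dose) = log(AUC) − log(dose). If every subject takes the nominal dose, log(dose) is constant within treatment. Normalising then moves only the treatment contrast, by ln(2000) − ln(1600) = ln(1.25) = 0.2231. Residuals, standard error and degrees of freedom stay the same. The estimate and both limits are multiplied by 1.25, and the log-scale width is unchanged.

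**5. Simulation of the stated design.** Four subjects, 2 residual degrees of freedom, true Frel = 1, 20,000 runs. The within-subject log-SDs are assumptions, since the protocol gives none.

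| Assumed log-SD | Planned ratio | Dose-normalised ratio | 90% CI coverage of Frel = 1, planned | Same, normalised |
|---|---|---|---|---|
| 0.3 | 0.80 | 1.00 | 81.5% | 90.2% |
| 0.6 | 0.80 | 1.00 | 87.9% | 90.0% |

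**6. Size against random error.** The half-width on the log scale is t(0.95, 2 df) × σ × √(2/4), with t = 2.920 and σ = √ln(1 + CV²). For assumed within-subject CVs of 20%, 30% and 50%, the 90% interval runs from the estimate divided by to the estimate multiplied by 1.51, 1.83 and 2.65. The dose factor of 1.25 is systematic, but smaller than any of these.

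**The case against.** Five points can be made for the plan.

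- **CL/F already carries the dose.** CL/F(tablet) divided by CL/F(solution) is (2000/AUC(tablet))/(1600/AUC(solution)) = 1.25 × R, which is the dose-normalised AUCinf ratio. This is true. But CL/F is only summarised descriptively: it lies outside the model and carries no confidence interval for the comparison. It also has no counterpart for AUClast or Cmax.
- **The SAP may add the step.** Section 8.1 leaves technical detail to a SAP, which is not at hand. But the protocol does not leave the response variables or the ratio open. It fixes both, twice, and labels the result.
- **Nothing is decided on this ratio.** The study is descriptive, with no hypothesis test, margin or bounds, and Part C starts in parallel with Part B. With four subjects the interval will be wide whichever ratio is used. The shift can also be undone afterwards by a known constant. All of this stands and limits the practical harm. It does not make the labelled quantity correct.
- **The unadjusted ratio is useful.** Given an absolute plasma target of 3–5 µM, exposure at the doses actually given is a legitimate comparison. This stands, and is why that ratio should be kept under its own label.
- **Dose-normalisation has its own assumption.** Section 2.1.2 makes saturation an open question for the solution. This also stands. For AUC the factor follows from the definition of relative bioavailability. Applying it to Cmax, or reading the result as a constant per-mg formulation effect, needs approximate dose-proportionality.

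**Conclusion.** The analysis is wrong as written. The statistic specified for Part B does not estimate the quantity named in the objective: for AUC it estimates 0.80 times that quantity, and the estimate and both confidence limits are low by a factor of 1.25. For Cmax the same factor applies only if Cmax is roughly proportional to dose up to 2000 mg, which the protocol does not establish.

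The defect is confined to the solution/tablet ratio. The fed/fasted ratio compares 1600 mg with 1600 mg. In practice the impact is moderate, because Part B is exploratory and imprecise and the error can be corrected afterwards. Settling the definition in advance still matters, since otherwise the choice between two ratios would be made after the results are known.

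**What to change.** In Section 8 and the synopsis, state that for Part B relative bioavailability will be estimated from log(Cmax/dose), log(AUClast/dose) and log(AUCinf/dose), using the dose actually administered, with the crossover model and 90% interval already planned. Keep the ratio of unadjusted Cmax and AUC as a second output, labelled as exposure at the administered doses (1600 mg solution against 2000 mg tablet). Add that the dose-normalised ratio assumes approximate dose-proportionality over this range, chiefly for Cmax. Leave the fed/fasted analysis as it is, and carry the same definitions into the SAP.

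The cost is about one sentence in each place. No extra data are needed, and no dose, sample size or schedule changes. The only downside is the reliance on proportionality, which showing both ratios makes visible.
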